### Sample size

The required sample size was estimated based on the primary outcome, dengue incidence in communities. Since the numbers of dengue cases in each school catchment area were unknown, the sample size is necessarily an estimate. This estimate was attained by using township level data from the two selected study townships. There was a total of 2,885 dengue cases in South Dagon and Shwepyithar townships during 2013–2018 giving an average of 480 cases/year during this period. Dividing the number of cases with the number of middle and high schools in these two townships gives a conservative estimate of 480/46=10.5 cases per school catchment area per year. We plan to recruit a minimum of about 40 students per school per year. The calculations would assume that in the control, the incidence is 10.5 dengue cases per 40 person-years of observation i.e., incidence rate of 0.26 dengue cases per person-year of observation and expect this to drop to approximately 0.18 dengue cases per person-year of observation in the intervention (i.e., 7.35 dengue cases per 40 person-years of observation). Using a cluster randomized design with 46 schools (23 schools per arm) and 10.5 cases per school catchment area at baseline, with α=0.05 this study has more than 80% power to detect an approximate 30% reduction in the dengue incidence rates between the control and the intervention arms. This estimate assumed an intra-cluster correlation coefficient (ICC) of 0.01. An intra-cluster correlation coefficient (ICC) for the dengue outcome is not available in the literature. We therefore used the next best available estimates, based on our previous assessment of ICCs for malaria prevalence and incidence in Myanmar which are low in this country, on average 0.003 (95% CI 0.000-0.010)
^
45
^. Although malaria is a different vector-borne disease with different transmission pattens in different settings, we think that the ICCs for malaria in Myanmar probably are the most realistic we can get and provide better estimates than unfounded guesses. The ICC is context-specific (location, spatial scale, etc.) and is preferred for studies with binary outcomes, such as this trial. As an additional guide, a reduction in dengue incidence by 25–30% would be consistent with the objectives of both the WHO Global Strategy for dengue prevention and control 2012–2020
^
46
^ and the WHO Global Vector Control Response 2017–2030
^
37

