### Randomization and blinding

Allocation of interventions will be done after baseline collections (described below). Of the 46 eligible schools, 23 will be allocated to the intervention arm and 23 to the control arm. This will be accomplished by an open public lottery event. At this event, representatives from each school will attend, including regional and township health and educational representatives, teachers, parents, and students. Information about dengue and the goals of the project will be given. The reasons for randomization, its procedures, and the concepts of intervention and control will be explained. Attendees will also have a chance to ask questions about dengue, vector control, health seeking behaviors, personal experiences of dengue, and specific details about the project. The lottery will be carried out as follows. Small pieces of paper, indistinguishable from one another, numbered from 1 to 46, will be folded and placed in non-transparent envelopes and mixed in a bowl. Each number represents a cluster (school) and a list of the schools with their respective number will be consulted during the process. A large screen with the numbered list of school names will be shown above the bowl, visible to everyone. A person not involved in the study, and accepted by all participants, will be selected to make the draw. Two flip boards with large sheets of paper will be placed on either side of the bowl with the heading ‘Intervention’ and ‘Control’ (in Burmese). The first number drawn (representing a specific school) will be assigned to the Intervention arm, the next number/school drawn will be assigned to the Control arm, and so on. Following the draw, the implications of being in either of the two arms will be discussed and the roles of participants, health volunteers, and sub-district hospital staff will be reviewed. By following this lottery scheme, the interventions are allocated at the same time as the sequence is generated, obviating the need for allocation concealment. At this meeting we will take care not to provide any information about planned dengue control interventions that will be used in the trial to participants from the control arm to minimize contamination between the groups. 

The study is unblinded for both participants and data collectors due to the nature of the intervention, e.g., it is not feasible to use placebo interventions of larvivorous fish.

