**Figure 2. f2:**
[figure not shown]
Time schedule of enrolment, interventions, and pre- and post-allocation data collections based on Standard Protocol Items: Recommendations for Interventional Trials (SPIRIT) checklist
^
48
^. Arrows indicate continuous activities. Dashed arrow indicates that some of the vector control interventions will continue until June Year 2. Primary and secondary outcome measures in parentheses; see
Table 2 for further details.

The secondary disease outcomes will be assessed by seroprevalence assessments in schools and households at baseline (June Year 1) and at two follow-ups (four and eight months after baseline) and seroconversions between these two time points. In each school, a total of 40 students, teachers and staff (20 randomly selected 6
^th^ grade students, 20 randomly selected students in grade 1–5 based on feasibility and financial reasons) will be asked to provide a finger prick blood sample for a dengue RDT. Similarly, seroprevalence will be assessed in 40 households per school catchment area of which 20 will be students’ households and 20 randomly selected households in each school catchment area. One randomly selected person (any age >1 year old) in each household will be selected. Thus, there will be 20*23 = 460 individuals in each group (6 graders, grades 1–5, student households and other households) which permits detection of a 30% difference in seroconversion between the two study arms allowing for a 10% dropout rate, with 80% power and 5% significance. The presence of dengue antibodies (IgG and IgM) will be confirmed by a finger prick blood sample of 10μL and a rapid diagnosis test (RDT) kit (SD BIOLINE Dengue IgG/IgM, Standard Diagnostic Inc., Korea). A seroconversion will be determined when an RDT negative person becomes positive in a subsequent collection. Written informed consent will be taken. Data on potential confounders, e.g., age, sex, residence, travel history, and previous dengue history will be collected for each person using a short case report form (CRF).

**
*Mosquito collections.*

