### Data analyses

**
*Effect of intervention on primary outcome*
**

1. 
**Dengue incidence rate in communities (DI).** The total cumulative number of dengue cases in the communities will be recorded passively through patients presenting at collaborating public hospitals and health centers in the two townships. Each case will be confirmed by dengue antigen/antibody RDTs. Each case that resides in the school catchment areas will be noted as such. The denominator will be the estimated population in each school catchment area. Data analysis for the primary outcome will be a comparison of the overall difference in incidence rate of confirmed dengue cases between the intervention and non-intervention school catchment areas with sub-analyses comparing the monthly incidence over time, before, during and after the interventions to examine the timing of any intervention impact. Incidence data will be collected continuously over a one-year period. At the cluster level, analysis will be by intention to treat, i.e., taking the trial arm as that to which, each cluster was randomized. At the individual level, people will be taken to have the allocation of the arm in which they are resident at the time of any data contributed. A flowchart showing numbers of clusters, and average numbers of households per cluster, over time will be constructed in accordance with Consolidated Standards of Reporting Trials (CONSORT) guidelines
^
66

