^. For the primary analysis, missing data may occur if complete clusters decline to continue in the trial. In this case, the cluster will still be included as long as any data on the primary outcome are available. This does introduce a risk of bias in estimating effectiveness, if loss of clusters is related to performance of the interventions. Dengue incidence in communities will be analyzed using a Poisson regression model. A negative binomial regression will be considered if there will be over-dispersion in the Poisson distribution. The response variable will be the number of dengue cases per cluster and the exposure will be the person-time at risk. Hence, the analysis will yield rate ratios. Multilevel models will not be used for this outcome since the number of cases may be too small for them to be fitted robustly. Statistical significance will be declared at 5% significance level. The 95% confidence intervals will be calculated and reported where applicable. A detailed statistical analysis plan (SAP) will be developed prior to database lock.

**
*Effect of intervention on secondary outcomes*
**

2. 
**Seroconversion rates in schools (SR
_S_).** The proportion of dengue antibody seroconversion in schools will be calculated as the number of seroconversions between the baseline and subsequent follow-ups at four and eight months after the implementation of the interventions divided by observation-days of school populations. The definition of seroconversion is when a participant has converted from being IgG (or IgM) negative during one sampling event to being IgG (or IgM) positive during a second sampling event. Dengue incidence based on seroconversions will be analyzed using a Poisson regression model. A negative binomial regression will be considered if there will be over-dispersion in the Poisson distribution. The response variable will be the number of dengue cases per cluster and the exposure will be the person-time at risk. Hence, the analysis will yield rate ratios. Multilevel models will not be used for this outcome since the number of cases may be too small for them to be fitted robustly.3. 
**Seroconversion rates in households (SR
_H_).** The proportion of dengue antibody seroconversion incidence in a selection of 40 households per school catchment area will be calculated and analyzed in the same way as for schools.4. 
**Mosquito Adult Index in schools (AI
_S_).** This the number of adult female
*Ae. aegypti* and

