*Aedes* mosquitoes were reduced in two community-driven integrated vector control interventions which included guppy fish, gravid-ovitraps, solid waste management, community education and engagement, and pyriproxyfen
^
74,
75
^. We believe that environmental risks, e.g., reduced biodiversity, of using guppy fish can be reduced by proper education on how to apply fish in containers in students’ homes. There is also an interesting educational component for students to understand biological concepts through fish breeding and development in school breeding aquaria.

Disease control interventions should be integrated and anchored in community processes, where schools could play important roles by engaging students, parents and teachers. By improving and/or adjusting school health curricula to include vector and disease control sessions, knowledge and behavioral change could be disseminated to communities by students
^
18,
76
^. Knowledge, attitudes, and self-efficacy of students for dengue prevention and control can be improved by using educational games, cartoons, observations, lectures and information campaigns
^
18
^. Since there is a lack of randomized controlled trials to assess the effect of school-based educational interventions on dengue and risk behaviors
^
18
^, our trial would contribute to this gap in knowledge. Health authorities in Myanmar are developing integrated training manuals and guidelines for community and school-based vector control, including the
*Aedes*-free school program
^
27
^.

Dengue transmission dynamics exhibit strong spatial and temporal variations
^
77–
79
^. Therefore, it is always difficult to assess the effect of dengue control interventions as they may fall in years with low and insufficient number of cases. Although we cannot predict future outbreak patterns, we have selected townships with the highest number of cases during the preceding years and where no other dengue interventions have been implemented. A longer intervention period would increase the likelihood of an outbreak year and avoid interepidemic periods, however, this will also reflect in costs and feasibility constraints. Another, limitation inherent in dengue research is the presence of relatively high proportions of asymptomatic cases, who, of course, will not show up in clinics and in national statistics.

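### The primary dengue model names no baseline covariate, although every cluster has dengue serology before allocation; pre-specifying one covariate costs little and may gain power

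*Protocol article*

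**What the plan says.** Under Data analyses, the primary outcome (DI) is modelled by Poisson regression, with negative binomial to be considered if the counts are over-dispersed. Multilevel models are ruled out. The model is then described so: "The response variable will be the number of dengue cases per cluster and the exposure will be the person-time at risk". Trial arm is implied; no baseline term is mentioned. The seroconversion outcomes in schools and households (SR_S, SR_H) get the same description. Pre-intervention incidence appears only in "sub-analyses comparing the monthly incidence over time, before, during and after the interventions".

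The mosquito indices are treated differently: additional analyses add the baseline value, in categories, as a covariate.

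On timing, Randomization and blinding states: "Allocation of interventions will be done after baseline collections (described below". Data collection lists what is gathered then: "The secondary disease outcomes will be assessed by seroprevalence assessments in schools and households at baseline (June Year 1". The sample is 40 people per school and one person in each of 40 households per catchment. The lottery is a single draw of 46 numbers assigned alternately to the two arms, with no stratification or matching.

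The Discussion acknowledges heterogeneity: "Dengue transmission dynamics exhibit strong spatial and temporal variations". A detailed SAP is promised before database lock.

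**The concern.** With 23 clusters per arm, differences in transmission between catchments add to the variance of the rate ratio. Nothing in the allocation balances them, so chance imbalance in local dengue risk passes into the estimate. A prognostic cluster-level measure taken before allocation can absorb part of this and cannot have been affected by arm. Such a measure exists in every cluster, and the protocol uses the same device for its mosquito outcomes but not for the outcome on which the trial was sized. At stake is precision on the primary comparison, if catchments differ more than the sample-size section assumes.

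**Working it through.** **Inputs.** From Sample size: "Using a cluster randomized design with 46 schools (23 schools per arm) and 10.5 cases per school catchment area at baseline"; "incidence rate of 0.26 dengue cases per person-year of observation" in the control arm; 7.35 cases per cluster under intervention (10.5 × 0.70); ICC 0.01; α = 0.05, taken as two-sided because the protocol does not say. Assumed, because the documents give neither: CVs above 0.17, and the correlation ρ between the baseline measure and the true cluster rate.

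**1. CV implied by the ICC.** k = √(ICC × (1 − p)/p) = √(0.01 × 0.74/0.26) = 0.169, about 0.17. This holds on the sample-size section's scale of 40 person-years per cluster. If the two townships' 594,000 people are divided by 46 (about 12,900 per catchment), p = 10.5/12,913 = 0.00081 and the same ICC gives k of about 3.5. The ICC therefore does not settle the CV.

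**2. The plan's own power.** The claim is "with α=0.05 this study has more than 80% power to detect an approximate 30% reduction". The cluster-rate formula on the count scale gives:

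- Counting noise: 10.5 + 7.35 = 17.85.
- Between-cluster part: k² × (10.5² + 7.35²) = 0.0285 × 164.27 = 4.68.
- Variance: v = 22.53.
- z = (10.5 − 7.35) × √(22/22.53) = 3.11.
- Power = Φ(3.11 − 1.96) = 87.6%.

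A two-proportion calculation with design effect 1 + 39 × 0.01 = 1.39 gives 93%. Both agree with the stated figure.

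**3. Adding a covariate.** A baseline covariate can shrink only the between-cluster part, by the factor (1 − ρ²). Poisson counting noise stays. With v = 17.85 + k²(1 − ρ²) × 164.27:

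| CV k | unadjusted | ρ = 0.5 | ρ = 0.7 |
|---|---|---|---|
| 0.17 (ICC 0.01) | 87.6% | 89.2% | 90.7% |
| 0.25 | 79.6% | 83.2% | 86.8% |
| 0.4 | 60.4% | 67.4% | 75.3% |
| 0.5 | 48.6% | 56.3% | 66.0% |

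The ceiling for a perfect covariate is v = 17.85, z = 3.50, power 93.8%.

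**4. Allowing for noise in seroprevalence.** The table treats the covariate as measured without error. A simulation (3,000 runs, dispersion-scaled Poisson, t reference) instead used observed seroprevalence in 40 people per school, with an assumed mean of 40% and an assumed between-school SD of 0.6 on the logit scale:

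| CV | ρ | unadjusted | adjusted |
|---|---|---|---|
| 0.17 | 0.5 | 87.0% | 87.4% |
| 0.17 | 0.7 | 87.3% | 89.2% |
| 0.4 | 0.5 | 61.9% | 67.0% |
| 0.4 | 0.7 | 61.5% | 72.6% |
| 0.5 | 0.5 | 49.8% | 55.8% |
| 0.5 | 0.7 | 51.5% | 62.1% |

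The gain is 0 to 2 points at the plan's CV. At CV 0.4 to 0.5 single settings range from 5 to 11 points; a repeat simulation put it at about 6 to 10. With no correlation, adjustment changed power by about 0 to −2 points.

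**5. Chance imbalance.** At CV 0.4, heterogeneity alone gives the log rate ratio a standard deviation of 0.4 × √(2/23) = 0.12, against a target of |ln 0.70| = 0.36, that is, about a third of it.

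**6. Which model the argument applies to.** Steps 2 to 4 assume that the standard error reflects over-dispersion. Under plain Poisson it does not: with no true effect, the simulated rejection rate was 22% at CV 0.4 and 46% at CV 0.8. A dispersion-scaled model at CV 0.4 rejected 4.8% of the time without the covariate and 5.5% with it.

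**The case against.** The strongest objection is that this rests on silence. The article gives response, exposure and model family, excludes no covariate, and defers detail to a SAP. A reader might infer that the model is meant to hold arm and person-time and nothing else; the text does not say so. Primary-unadjusted with additional adjusted analyses is also a respectable order, and it is the one used for the mosquito indices. That stands as a limit on the claim. It does not remove the point: the protocol names baseline adjustment where it intends it, and not here. The SAP is due only before database lock, in a trial unblinded to data collectors. A covariate first named after cases have accrued is less well protected than one named now.

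A reader might also infer that power is certainly lost. The documents do not support that. On the protocol's ICC the gain is 0 to 2 points and power exceeds 80% either way. The larger gains need a CV and a correlation found nowhere in the text; the Discussion calls spatial variation strong without quantifying it. Multiplying the whole variance by (1 − ρ²) would suggest power near 95% at CV 0.17 with ρ = 0.5, but that exceeds the 93.8% ceiling for a perfect covariate.

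Finally, seroprevalence reflects accumulated past exposure, whereas the outcome is one year of passively detected clinical cases. It is a proxy, and its correlation with incidence could be weak. That objection stands in full and sets the downside.

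**Conclusion.** The point holds as a modest, conditional one. The described DI, SR_S and SR_H models name no baseline covariate, although serology from every cluster precedes an unstratified lottery. Adjusting for it would bring about 0 to 2 points of power at the protocol's implied CV of 0.17, and about 6 to 10 points if the CV is 0.4 to 0.5 and the underlying correlation 0.5 to 0.7, both assumed. In the second case unadjusted power would be only about 50% to 62%, so the recovery would matter.

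That unexplained cluster variation widens the error is true of a negative binomial or dispersion-scaled model. Under plain Poisson, the first-named model, the same variation makes standard errors too small. The covariate lessens that fault but does not cure it.

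**What to change.** State in the DI, SR_S and SR_H models that one cluster-level covariate is included: the logit of June Year 1 dengue seroprevalence in the cluster's baseline sample, with a continuity correction for clusters at 0% or 100%. Say which people make up that sample and apply the same definition in every cluster. Report the unadjusted rate ratio as a sensitivity analysis. Settle this before outcome data accrue. Baseline seroprevalence is preferable to the pre-intervention case count, which may cover only a short window and be mostly noise. Keep the variance robust to over-dispersion, since the covariate does not replace that.

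The cost is a sentence of wording and one of 44 residual degrees of freedom (46 clusters less two parameters), with no new data. If seroprevalence proves unrelated to incidence, the loss is up to about 2 points of power.

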### Outcomes

The primary outcome is dengue incidence rates in communities (
Table 2)

**Table 2. T2:** Primary and secondary outcome measures and other outcomes. Baseline is June when school starts in Myanmar. (Y1=Year 1, Y2=Year 2).

Outcome	No.	Name	Index	Description	Unit	Frequency of data collection	Details
Primary outcome	1	Dengue incidence rate in communities	DI	Confirmed number of dengue cases (numerator) and the estimated population in each school catchment area (denominator) during study period	No. cases during study period / population	Continuous	Passive case detection assessed using dengue rapid diagnosis tests (RDT) in public hospitals and health centers
Secondary outcomes	2	Seroconversion rates in school children	SR _S_	Seroconversion rates between two time points in students at school	No. of seroconversions / no. observation-days	3 times: - Jun. Year 1 (baseline), - Oct. Year 1, - Feb. Year 2.	Seroconversion rates assessed by dengue rapid diagnosis tests (RDT)
	3	Seroconversion rates in households	SR _H_	Seroconversion rates between two time points in 20 households in communities	No. of seroconversions / no. observation-days	3 times: - Jun. Year 1 (baseline), - Oct. Year 1, - Feb. Year 2.	Seroconversion rates assessed by dengue rapid diagnosis tests (RDT)
	4	Mosquito adult index in schools	AI _S_	Mean number of adult female *Ae.* *aegypti* and *Ae. albopictus* per school collected indoors and outdoors	No. / school	4 times: - Jun. Year 1 (baseline), - Oct. Year 1, - Feb. Year 2, - Jun. Year 2.	Mosquito collections using a battery- driven mechanical aspirator.
	5	Mosquito adult index in households	AI _H_	Number of adult female *Ae. aegypti* and *Ae. albopictus* per school or house collected indoors and outdoors	No. / household	4 times: - Jun. Year 1 (baseline), - Oct. Year 1, - Feb. Year 2, - Jun. Year 2.	Mosquito collections using a battery- driven mechanical aspirator.
	6	Breteau index in schools	BI _S_	No. of *Aedes* positive containers per 100 schools	No. / 100 schools	4 times: - Jun. Year 1 (baseline), - Oct. Year 1, - Feb. Year 2, - Jun. Year 2.	Mosquito collections in schools
	7	Breteau index in households	BI _H_	No. of *Aedes* positive containers per 100 houses	No. / 100 houses	4 times: - Jun. Year 1 (baseline), - Oct. Year 1, - Feb. Year 2, - Jun. Year 2.	Mosquito collections in households

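### The two seroconversion outcomes have two event rules that classify some people differently, and two denominators that are not reconciled.

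*Protocol article*

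**What the plan says.** All references are to the protocol article.

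**Event.** Data collection, under Disease surveillance: "A seroconversion will be determined when an RDT negative person becomes positive in a subsequent collection". The test reads two markers: "The presence of dengue antibodies (IgG and IgM) will be confirmed by a finger prick blood sample". Data analyses, item 2 (SR_S), says instead that a participant has "converted from being IgG (or IgM) negative during one sampling event to being IgG (or IgM) positive during a second sampling event".

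**Denominator.** Table 2 gives the unit for both outcomes as "No. of seroconversions / no. observation-days". Data analyses, item 2, has the number of seroconversions "divided by observation-days of school populations". The same item then describes the Poisson or negative binomial model: "The response variable will be the number of dengue cases per cluster and the exposure will be the person-time at risk". It does not define who is at risk.

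**Households.** Item 3 says that SR_H "will be calculated and analyzed in the same way as for schools", so both outcomes carry the same wording.

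**Size.** Data collection: "Thus, there will be 20*23 = 460 individuals in each group". This is said to detect a 30% difference with 80% power at 5% significance, allowing for 10% dropout.

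**The concern.** A seroconversion rate needs an event rule and a matching risk set: whoever can become an event contributes time, and nobody else does. Here neither is fixed.

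People already antibody-positive at baseline should be expected. The eligibility criteria in Table 1 do not select on serostatus, the townships were chosen for high dengue incidence, and household participants may be any age above one year. How these people are handled therefore decides who counts as an event and whose time is counted.

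For one group the choice also affects what the outcome means. Someone IgM-positive and IgG-negative at baseline who later shows IgG may be displaying the later course of an infection acquired before the intervention began. One rule counts that as a trial event and the other does not.

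**Working it through.** **1. The two event rules side by side**

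| Baseline | Later sample | Whole-test rule (Data collection) | Marker rule (Data analyses) |
|---|---|---|---|
| IgG−, IgM− | either marker + | event | event |
| IgG+, IgM− | IgM turns + | not an event (already positive) | event |
| IgM+, IgG− | IgG turns + | not an event (already positive) | event |
| IgG+, IgM− | unchanged | not an event | not an event on the natural reading |

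The rules disagree in rows two and three.

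**2. How far the event count could move (illustration)**

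Assume 460 people, a baseline seropositive share s, and 10% converting on some marker whatever their baseline status. This takes every baseline positive to be positive on one marker only, so the gap shown is an upper one.

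- Marker rule: 460 × 0.10 = 46 events.
- Whole-test rule: 460 × (1 − s) × 0.10, which is 36.8 at s = 0.2, 23 at s = 0.5 and 9.2 at s = 0.8.

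**3. Dilution of the reported rate**

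Under the whole-test rule only a share 1 − s can convert. Dividing by everyone's days gives about the true rate × (1 − s): factors of 0.8, 0.5 and 0.2 at s = 0.2, 0.5 and 0.8.

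**4. Rate ratio, only if unrestricted days were the model exposure**

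Under the whole-test rule, observed ratio = true ratio × (1 − s in intervention) / (1 − s in control).

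- Equal shares: the ratio is unchanged.
- s = 0.55 intervention, 0.45 control: 0.70 × 0.45/0.55 = 0.57.
- Shares reversed: 0.70 × 0.55/0.45 = 0.86.

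How large an arm difference chance could produce depends on assumptions: half the sample seronegative, and the ICC of 0.01 that the Sample size section uses for the primary outcome. The school sample is 40 per school, so 40 × 23 = 920 per arm, with design effect 1 + 39 × 0.01 = 1.39.

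- SE of the difference in seronegative share = √(2 × 0.25 × 1.39/920) = 0.027; 95% range ±0.054.
- A 47.3% against 52.7% split gives 0.70 × 0.473/0.527 = 0.63, or 0.70 × 0.527/0.473 = 0.78.

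Is that bias? I simulated no intervention effect with 920 per arm, half seronegative, 10% or 27% of seronegatives converting, no clustering, and everyone in the denominator. The geometric-mean ratio was 1.00. The two-sided Poisson test rejected in 4.2% and 3.4% of runs, below the nominal 5%. The imbalance adds noise but does not shift the estimate.

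**5. The plan's power statement**

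20 × 23 = 460 checks. The 80% power cannot be reproduced, because no control seroconversion proportion is given. Working backwards with 460 × 0.9 = 414 per arm, a two-sided 5% test and a 30% relative reduction, 80% power needs a control proportion of about 27.4% (31.2% with ICC 0.01 and 20 per cluster). Holding 27.4% fixed, ignoring clustering and limiting the analysis to seronegatives:

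| Assumed s | At risk per arm | Power |
|---|---|---|
| 0 | 414 | 80% |
| 0.2 | 331 | 71% |
| 0.4 | 248 | 58% |
| 0.5 | 207 | 51% |
| 0.8 | 83 | 24% |

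**The case against.** The strongest reply is that the rate ratio comes from the regression, whose stated exposure is already person-time at risk; observation-days would then only describe the reported rate and its unit. That stands. A reader might infer that the treatment comparison is biased by putting everyone in the denominator. The text does not support this: it nowhere says that all days enter the model. Even if they did, randomisation gives equal expected seronegative shares, so the result is chance error.

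A reader might also infer that someone stably IgG-positive and IgM-negative could count as an event by being IgM-negative first and IgG-positive second. That needs a strained reading across markers. The natural reading compares like with like, and such a person has converted on nothing. The conflict in rows two and three of the table does not depend on it.

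Two further replies are fair. The introduction says that a person can contract dengue up to four times, so new IgM in an IgG-positive person may be a genuine new infection, and the marker rule is not absurd. Baseline rapid tests are also already planned, so serostatus will be known for those sampled.

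Timing conventions within an interval can be left to the statistical analysis plan. Two rules that disagree in the same article cannot be treated as omitted detail. Because that plan is due only before database lock in an unblinded trial, the choice could be made with results by arm in view.

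**Conclusion.** The point holds as an internal contradiction affecting two secondary outcomes. The event rules classify differently anyone positive on a single marker who later turns positive on the other. The rate formula and the model use differently worded denominators, and the risk set is undefined. Followed as written, the rate formula dilutes the reported rates relative to the whole-test rule; the modelled rate ratio is not shown to be biased.

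The size cannot be taken from the document, since no baseline seroprevalence is stated. Every figure that depends on a seropositive share is illustrative: at an assumed 50%, reported rates would be halved and the event count could differ by up to a factor of two between the rules. The primary outcome, incidence of passively detected cases in communities, is unaffected. The contradiction should be corrected before the protocol is reused, as it is offered for future implementation.

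**What to change.** State one event rule, in the same words, in Table 2, Data collection and Data analyses. One workable form: negative on both IgG and IgM at the previous sample, then positive on either. Use one denominator for both the reported rate and the model: person-time of people negative by that rule, ended at conversion. Apply both to SR_S and SR_H, and report baseline seroprevalence by arm. New IgM positivity in people already IgG-positive may be reported separately.

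The change is one of wording and uses baseline tests already planned. The cost is a smaller risk set than 460 per group. The power statement in Data collection deducts only 10% dropout, so it should be restated on the expected number of seronegatives, giving the assumed seroprevalence and control seroconversion proportion.
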